### The casefinder study

After one day of training on the clinical characteristics, presentation and course of dementia, community key informants will generate, from their knowledge of the local population names of those living in the catchment areas to be surveyed, who they think may be possibly or probably suffering from dementia. Key informants may be community health workers, social welfare officers, community activists or other volunteers depending upon the local health system. The aim is to identify where possible the cadre of workers with a community outreach role and some consequent knowledge of the circumstances of all or many of the local inhabitants. These assessments will then be validated against the comprehensive structured clinical diagnostic assessment from the subsequent cross-sectional survey. The sensitivity, false positive rate, and positive and negative predictive values of the dementia case-finding procedure will be estimated with respect to the criterion of the structured clinical research diagnosis. The characteristics of those with research dementia diagnoses who were and were not nominated by community key informants will be compared to identify factors predicting failure of detection. Factors to be assessed include age, gender, marital status, living circumstances, socio-economic status, rural or urban residence, recent use of health services, severity of dementia, subtype of dementia, co-morbidity, associated behavioural problems, time spent caregiving, caregiver strain and mental health status. A sample of 2,000 in each centre will provide approximately 90 cases of dementia allowing sensitivity to be estimated with a precision of +/- 7%, and a difference in sensitivity between (for example) rural and urban areas of 30% (80% vs 50%) to be detected with 95% confidence and 80% power.

### The 10/66 caregiver education and training intervention

The 10/66 intervention was developed in India (for use by multi-purpose health workers), but with input from the wider 10/66 group including developed country experts. It targets the main carer, but includes members of the extended family. The aim is to provide basic education about dementia and specific training on managing problem behaviours. The three simple, manualised modules are delivered over five, weekly, half hour sessions.

#### Module 1. Assessment – 1 session

a) Cognitive/functional impairment b) Carer's knowledge and understanding of dementia. c) Care arrangements (Who are the family members? Who lives with the person with dementia? How do they assist the main carer? Which behavioural problems present most difficulties? How burdened do they feel?).

#### Module 2. Basic education – 2 sessions

a) general introduction to the illness. b) what to expect in the future c) What causes/does not cause dementia? d) locally available care and treatment.

#### Module 3. Training on problem behaviours – 2 sessions

Problem behaviours identified in the assessment are addressed (personal hygiene, dressing, incontinence, repeated questioning, clinging, aggression, wandering, apathy). After extensive piloting the intervention is now supported by a structured, manualised two day training program for MPHWs comprising a) basic knowledge about dementia, b) assessment skills, c) basic counselling skills and d) role playing of intervention scenarios.

In Argentina, Mexico, Peru, Venezuela, Russia, and China, we are carrying out a formal randomised controlled trial; all people with dementia identified in the population-based survey (and their carers) will be offered randomisation to receive the caregiver training and education intervention either a) immediately or b) after 6 months, that is after the final outcome assessments will already have been completed. The inclusion criterion is a 10/66 algorithm diagnosis of dementia. Exclusion criteria are serious intercurrent illness in the person with dementia, or absence of family caregivers. Consent is obtained from the person with dementia, where possible, and their principal caregiver. The principal caregiver is the family member or close friend who is most involved in providing and/or organising care for the person with dementia. Paid caregivers and/or other family caregivers may participate in the intervention but are not subject to the outcome assessment. In the pre-randomisation visit, a research worker completes the baseline assessments (see below), explains the trial and seeks informed consent from the person with dementia and the caregiver. Randomisation is carried out in London, and the codes transmitted to the local 10/66 centre by fax or e-mail. Randomisation is by permuted block to ensure in each centre an even distribution of baseline caregiver strain. The intervention in all centres will be evaluated in terms of uptake rates, completion rates and satisfaction rates (among caregivers), together with before (baseline) and after (six months) intention to treat comparisons of standard assessments. Principal outcomes related to the caregiver are caregiver role strain (Zarit caregiver burden interview), psychological distress (SRQ 20), and quality of Life (the 17 item WHO-QoL Bref) [101]. Principal outcomes related to the person with dementia are behavioural and psychological symptoms of dementia (Neuropsychiatric Inventory – NPI-Q) [80] and quality of life (DEMQoL) [102].

The clinician (if any) responsible for clinical care of the person with dementia will be blind to the intervention. They may organise any supplementary care that they feel is indicated. The assessor, assessing outcome after the intervention will be blind to the intervention. The family, and the assessor will be asked to do everything they can to maintain blindness. Primary endpoint analysis will be according to intention to treat with last observation carried forward for missing data. Failures of randomization would be adjusted for as factors or covariates, using generalized linear modelling. In each centre, with 30 families randomised to the control and intervention arms, the study is powered to detect moderate effect sizes (0.8 or greater for change scores on continuously distributed outcomes) associated with the intervention, at 80% power and 95% confidence. Data from the different centres would be subject to meta-analysis. (ISRCTN41039907; ISRCTN41062011; ISRCTN95135433; ISRCTN66355402; ISRCTN93378627; ISRCTN94921815).

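### The caregiver trial lists five equal principal outcomes without saying which is the primary endpoint, and its only power statement is per centre for an effect of 0.8 that it calls moderate

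*Protocol article*

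**What the plan says.** The trial is described in the paragraphs after Module 3 of 'The 10/66 caregiver education and training intervention'.

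- **Outcomes.** For the caregiver: "Principal outcomes related to the caregiver are caregiver role strain (Zarit caregiver burden interview), psychological distress (SRQ 20), and quality of Life" (the WHO-QoL Bref). For the other member of the pair: "Principal outcomes related to the person with dementia are behavioural and psychological symptoms of dementia" (the NPI-Q), together with "quality of life (DEMQoL"). That makes five, all called principal and none ranked above another.
- **Primary analysis.** "Primary endpoint analysis will be according to intention to treat with last observation carried forward for missing data". No outcome is named in that sentence or near it.
- **Setting.** "In Argentina, Mexico, Peru, Venezuela, Russia, and China, we are carrying out a formal randomised controlled trial". Six registration numbers are listed.
- **Power.** The sample size is given per centre: "In each centre, with 30 families randomised to the control and intervention arms". For change scores, with 80% power and 95% confidence, the claim is that "the study is powered to detect moderate effect sizes (0.8 or greater").
- **Pooling.** "Data from the different centres would be subject to meta-analysis". Nothing is said about whether this is the main analysis, or what effect it could detect.

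**The concern.** A primary endpoint analysis needs a primary endpoint. With five outcomes of equal rank, the choice of which one the word refers to stays open until results are seen. Unless that is settled, the 95% confidence in the power sentence applies to each outcome separately and not to the conclusion that the intervention works.

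The power statement adds a second difficulty. By the usual convention a standardised effect of 0.5 is moderate and 0.8 is large. A reader who relies on the adjective would take a null result in one centre as evidence against a moderate benefit, which 30 families per arm may not provide. The analysis that could provide it, the pooled one, is mentioned in a single sentence without status or power.

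**Working it through.** **Inputs from the article:** five principal outcomes; six countries; 30 families; effect 0.8 on change scores; 80% power; 95% confidence.

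**Assumptions added here:** two-sided 5% tests, 1:1 allocation, 30 read as per arm, no loss. Correlations among outcomes are not given, so a range is used.

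**1. The plan's own power figure.** Normal approximation: n per arm = 2(1.96 + 0.842)² / 0.8² = 15.70 / 0.64 = 24.5, so 25 (26 by the t distribution). Thirty per arm gives more than the stated 80%: 87% by the normal approximation, 86% by t. On this reading the statement is conservative. The sentence could also mean 30 families in total; 15 per arm gives about 56% power for 0.8 (t), so the stated 80% would not hold. The per-arm reading is the one that fits.

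**2. What one centre can detect (30 per arm, t distribution).**

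| Quantity | Result |
|---|---|
| Detectable effect at 80% power | 0.74 |
| Power for 0.8 | 86% |
| Power for 0.5 | 48% |
| Families per arm for 80% power at 0.5 | 64 |

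Effects are in standard deviations of the change score, the scale the article uses.

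**3. Five outcomes, each tested at 5%.** If independent: 1 − 0.95⁵ = 0.226. For equally correlated outcomes, by simulation of 400,000 sets of five test statistics:

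| Assumed correlation | Chance of at least one false positive |
|---|---|
| 0 | 23% |
| 0.3 | 21% |
| 0.5 | 18% |
| 0.7 | 15% |

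The figures do not depend on sample size, so they hold in one centre and equally in one pooled analysis of the five outcomes.

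**4. The planned meta-analysis.** If all six centres reach 30 per arm, there are 6 × 30 = 180 per arm. With a common effect:

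- Detectable effect at 80% power: (1.96 + 0.842) × √(2/180) = 2.802 × 0.1054 = 0.30.
- Power for 0.5: 99.7%.

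If effects differ between centres, the standard error of the pooled effect is √[(2/30 + τ²)/6], where τ is the between-centre standard deviation (assumed, as the article gives none). Power for 0.5 is then 99%, 96% and 87% at τ = 0.1, 0.2 and 0.3. If 30 is a centre total (90 per arm pooled, common effect), the detectable effect is 0.42 and power for 0.5 is 92%.

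**5. The scale of the effect.** The standard deviation of change equals the raw standard deviation × √[2(1 − r)], where r is the correlation between baseline and six months. The article does not give r.

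| Assumed r | 0.8 change-score SD, in raw SD | Power for 0.5 raw SD, 30 per arm |
|---|---|---|
| 0.3 | 0.95 | 36% |
| 0.5 | 0.80 | 48% |
| 0.7 | 0.62 | 69% |
| 0.8 | 0.51 | 85% |

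**The case against.** **Condensation.** This is a programme article that gives the trial two paragraphs. A multiplicity procedure and a meta-analysis model are commonly left to the full protocol or the analysis plan, neither of which is shown, and their absence alone would be no finding. That stands. It does not cover the primary endpoint: the article itself ranks the outcomes, gives five the same rank, and then refers to a primary endpoint that the ranking does not identify.

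**The adjective.** The number 0.8 is printed beside the word moderate, so the design value is not hidden. The article also says change scores, and step 5 shows that with r near 0.8 the effect is close to 0.5 on the raw scale, where moderate would be fair. This stands in part: the label can be defended only with a correlation the article does not state, and at r of 0.5 or below it cannot.

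**Stronger readings that the text does not support.**

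- A reader might infer that the trial will miss moderate effects. That is true of one centre on the change-score scale. It is not true of the programme, because a meta-analysis is planned and would have ample power under the stated assumptions.
- A reader might count five outcomes in six centres as 30 chances of success, giving 1 − 0.95³⁰ = 79% if independent. The article states no success rule, and six registrations fit six separate trials. The figure applies only if every centre's tests are read as confirmatory claims of one family.
- A reader might conclude that the primary analysis is set per centre and that the pooled one is demoted. Only the power sentence is tied to the single centre. The primary analysis sentence is not, and the order of sentences is not a ranking.

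**Choice of outcome.** Preferring the Zarit score is a judgement. One outcome per domain, or all five with adjustment, would also answer the point.

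**Conclusion.** The point holds in a limited form. The primary endpoint is not identified among five equal principal outcomes. If any one of them may count as success at 5%, the false-positive chance is 15–23% over the correlations considered, and pooling does not lower it. That range depends on the any-one-counts reading, which the article neither adopts nor excludes.

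The power statement is not wrong as arithmetic if 30 is per arm, but its label is doubtful and it describes only the weaker of the two analyses. A single centre has roughly an even chance of detecting 0.5 change-score standard deviations. The pooled analysis does not share that weakness, given full recruitment, no loss and a common effect, yet the article does not say that it is the decisive test. The matter should be corrected; it does not undermine the design.

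**What to change.** Make these changes before unblinding:

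1. Name one primary outcome and call the other four secondary. The Zarit score at six months is a natural candidate, because randomisation is already balanced on caregiver strain. Alternatively, keep all five and apply a Holm rule.
2. State that the centre-stratified pooled estimate is the primary test, with its detectable effect (about 0.30 for a single outcome tested at 5%) and the assumptions behind it, and that centre results are supportive. If the Holm rule is chosen, work out the pooled power at the adjusted levels: at 1%, the strictest step for five outcomes, the detectable effect is about 0.36.
3. Replace moderate by large, or give the effect on the raw-score scale with the assumed baseline-to-six-month correlation.
4. Say that 30 is the number of families per arm.

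The cost is wording. No further families are needed. The downside is that, if one primary outcome is named, the other four lose equal status, and single-centre results no longer stand as main results.

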##### 1) Outcome – The diagnosis of dementia

Our previously published 10/66 dementia diagnosis algorithm [5] requires

(i) A structured clinical mental state interview, the Geriatric Mental State, which applies a computer algorithm (AGECAT)[74], identifying organicity (probable dementia), depression, anxiety and psychosis and,

(ii) A cognitive test battery comprising a) the Community Screening Instrument for Dementia (CSI'D') COGSCORE [75] (incorporating the CERAD animal naming verbal fluency task), and b) the modified CERAD 10 word list learning task with delayed recall [76] and

(iii) An informant interview the CSI'D' RELSCORE [75], for evidence of cognitive and functional decline

(iv) an extended informant interview, the History and Aetiology Schedule – Dementia Diagnosis and Subtype (HAS-DDS), a modification of the earlier HAS [77], providing more detailed information on onset and course of a possible dementia syndrome

v) The NEUROEX, a brief fully structured neurological assessment with objectified quantifiable measures of lateralising signs, parkinsonism, ataxia, apraxia and primitive 'release' reflexes [78,79].

(vi) Behavioural and Psychological symptoms of dementia (BPSD); assessed using an informant questionnaire, the Neuropsychiatric Inventory (NPI-Q) [80].

Final dementia diagnoses is made in two ways. The main dementia outcome is defined as those scoring above a cutpoint of predicted probability of DSM IV Dementia syndrome [81] from the logistic regression equation developed in the 10/66 international pilot study, using coefficients from the GMS, CSI-D and 10 word list learning tasks [5]. The second approach involves the direct application of research diagnostic criteria for DSM IV and for the following dementia subtype diagnoses; NINCDS-ADRDA Alzheimer's disease criteria [82], NINDS-AIREN vascular dementia criteria [83], and Lewy Body Dementia [84]. The clinical assessment identifies other prevalent conditions relevant to the differential diagnosis of dementia and dementia sub-type: psychosis, depression, anxiety disorder, alcoholism, epilepsy and stroke. Circularity in further validation of these diagnoses can only be avoided by focusing upon their predictive validity. Thus, a diagnosis of dementia should lead to further cognitive and functional decline, and not recovery.

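### With outcomes assessed only at baseline and six months, last observation carried forward scores every missing outcome in the caregiver trial as exactly zero change

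*Protocol article*

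**What the plan says.** The trial is described in the protocol article's section on the caregiver education and training intervention, in the text after Module 3. The missing-data rule is fixed there for the primary analysis: "Primary endpoint analysis will be according to intention to treat with last observation carried forward for missing data".

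The same text sets the assessment schedule. Baseline measures are taken at a visit before randomisation. The intervention is then judged by "before (baseline) and after (six months) intention to treat comparisons of standard assessments". The delayed arm receives the intervention "after 6 months, that is after the final outcome assessments will already have been completed". No assessment between these two times is described.

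There are five principal outcomes. Three concern the caregiver (Zarit burden, SRQ 20, WHO-QoL Bref) and two the person with dementia (NPI-Q, DEMQoL). The power statement is framed on change scores. Centres are to be combined by meta-analysis. No trial dropout rate is given, and no other method for missing trial outcomes.

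**The concern.** Last observation carried forward needs an observation after randomisation if it is to carry any information about the course on study. Here there is none, so the rule amounts to baseline carried forward. Each family without a six-month score is given a change of zero, with no uncertainty attached, and is then counted like a family that was actually assessed.

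Two things are at stake. The first is the estimate and its interval: zeros in both arms pull the difference towards nothing and make the standard error too small. The second is the comparison itself. If the arms lose different fractions of families and the outcome drifts over six months, the zeros alone create a difference between arms. Pooling centres shrinks the standard error but does not remove such a bias.

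**Working it through.** **The plan's own figure.** The article gives no number on missing trial data. Its only trial figure is 80% power for an effect of 0.8 with 30 families. A two-sided 5% normal calculation gives 87.3% at 30 per arm and 59.1% at 15 per arm; 80% power needs 25 per arm. The stated 80% fits 30 per arm only with an unstated loss allowance of about 15% (25/0.85 = 29.4, rounded up to 30). That mismatch is a separate matter, and the present point does not depend on it.

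**Inputs.** From the article: the LOCF rule, two assessment times, change scores, six trial countries, and 30 families per centre, read here as 30 per arm. Assumed, because not stated: loss fractions dC and dT (control, intervention), mean changes mC and mT with worsening positive, SD of change 1 in each arm, and the same mean change in lost families as in those seen. The cohort follow-up table uses 15% non-response and 6% annual mortality. These are not trial figures and serve only as context for the range.

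**Formulae.** A missing change is set to 0, so in each arm:
- mean = (1 − d)·m
- variance = (1 − d) + d(1 − d)·m²
- LOCF standard error = √[(varC + varT)/n], with n all randomised per arm
- standard error from observed scores only = √[2/(n(1 − d))]

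If a baseline-adjusted model were fitted to the carried-forward scores, the same values would enter and the expected difference would be the same, since randomisation balances baseline in expectation.

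**Equal loss, true difference 0.80.** The expected LOCF difference is 0.80·(1 − d).

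| Loss in both arms | LOCF estimate | LOCF power, 30/arm | Observed-score power, 30/arm |
|---|---|---|---|
| 10% | 0.72 | 83% | 84% |
| 15% | 0.68 | 80–81% | 81.5% |
| 20% | 0.64 | 77–78% | 79% |
| 30% | 0.56 | 70–72% | 74% |

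For the interval, take stable controls and a change of −0.8 with intervention. At 15% loss and 30 per arm:
- varC = 0.85
- varT = 0.85 + 0.15 × 0.85 × 0.64 = 0.9316
- LOCF standard error = √(1.7816/30) = 0.244
- observed-score standard error = √(2/25.5) = 0.280

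The bias is 0.80 − 0.68 = 0.12. Coverage of the nominal 95% interval is then about 92% at 30 per arm and 77% at 180 per arm pooled. At 30% loss it is about 81% and 26%.

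**Equal loss, no true effect.** The bias is m·(d − d) = 0, so type I error stays at about 5%.

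**Unequal loss, no true effect, common change m.** The false difference has size m·|dT − dC|. If outcomes worsen, it favours the arm that loses more; if they improve, the arm that loses less.

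Worked case: m = 0.5, dT = 25%, dC = 10%.
- Bias = 0.5 × 0.15 = 0.075
- varC = 0.90 + 0.10 × 0.90 × 0.25 = 0.9225
- varT = 0.75 + 0.25 × 0.75 × 0.25 = 0.7969
- Standard error at 30 per arm = √(1.7194/30) = 0.239, z = 0.313, type I error 6.1%
- Standard error at 180 per arm = 0.098, z = 0.767, type I error 12.0%

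| Common worsening | Loss, intervention vs control | False difference | Type I, 30/arm | Type I, 180/arm pooled |
|---|---|---|---|---|
| 0.5 SD | 15% vs 10% | 0.025 | 5.1% | 5.7% |
| 0.5 SD | 25% vs 10% | 0.075 | 6.1% | 12.0% |
| 0.2 SD | 25% vs 10% | 0.030 | 5.2% | 6.1% |

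If the 30 families are a total (15 per arm, 90 per arm pooled), the 12.0% becomes 8.4%.

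**The case against.** The best defence is that the practical harm is modest. With equal loss the estimate and its standard error shrink together, so the test hardly changes: at 15% loss, power is 80–81% against 81.5% from observed scores. The remaining error is towards no effect, which many would call conservative. That stands for the test. It does not stand for the estimate and interval, which are what a meta-analysis uses, nor for unequal loss, where LOCF is not conservative in any fixed direction.

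The larger type I figures can also be challenged, rightly. They need a sizeable drift, a marked loss imbalance, 30 per arm and, for 12%, the same imbalance in the same direction in all six centres. If directions differ between centres the biases partly cancel.

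A reader might infer that zero change is a favourable value because dementia progresses. The article does say that "a diagnosis of dementia should lead to further cognitive and functional decline, and not recovery", but that concerns cognition and function, which are not among the five principal outcomes. Three of those are caregiver measures that need not worsen steadily, and no passage says that any of the five worsens over six months. The supportable statement is narrower: zero change has no support in the article.

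A reader might also infer that deceased participants are to be scored as stable. The article does not say so. Its wording covers missing data without an exception for death, so the handling is open rather than stated.

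Finally, with no assessment between baseline and six months, multiple imputation from baseline variables adds little to a baseline-adjusted model on observed scores. That is correct, and either is acceptable as the primary method.

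**Conclusion.** The point holds. It rests on two explicit statements, the LOCF rule and the two-assessment schedule, and is not a detail left to an analysis plan, because the article itself fixes the rule for the primary analysis. An interim visit that the article does not report would weaken it, but none is described.

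The firm consequence is attenuation by the missing fraction, with an interval too narrow around the attenuated value. The conditional consequence is a false difference equal to the common change times the difference in loss, in either direction. At a single centre the resulting inflation of type I error is small in the scenarios tabulated. It reaches about 12% only when pooled under the adverse assumptions listed. The article does not support reading this as a bias in favour of the intervention, or 12% as the expected error rate. This should be fixed, but the documents do not show it to be fatal to the trial.

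**What to change.** Replace LOCF as the primary method with a baseline-adjusted comparison of six-month scores under missing at random. This can be a baseline-adjusted model on the observed scores, or multiple imputation within arm using baseline scores and centre. State that baseline is not carried forward for outcomes of the person with dementia after death, and report deaths and other losses by arm.

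Add a delta-adjusted sensitivity analysis for data missing not at random. It is needed because the article's own remarks under Methodological issues, made about two-phase surveys, treat attrition among people with probable dementia as informative. LOCF may be kept as a sensitivity analysis only.

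The cost is a change of wording, a little programming and somewhat wider intervals (for example a standard error of 0.280 instead of 0.244 at 15% loss and 30 per arm). No new data are needed.

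### Covariate adjustment in the caregiver trial depends on an undefined failure of randomisation, so by implication the default analysis omits the baseline score and the strain balancing factor

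*Protocol article*

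**What the plan says.** All the relevant text is in the protocol article, in the trial description that follows Module 3 under the heading on the 10/66 caregiver education and training intervention.

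- **Baseline data.** "In the pre-randomisation visit, a research worker completes the baseline assessments (see below"), so each outcome has a score taken before allocation.
- **Allocation.** "Randomisation is by permuted block to ensure in each centre an even distribution of baseline caregiver strain". Strain, measured by the Zarit interview, is also one of five principal outcomes. The others are the SRQ-20, WHO-QoL Bref, NPI-Q and DEMQoL.
- **Comparison.** The text promises "before (baseline) and after (six months) intention to treat comparisons of standard assessments".
- **Analysis.** "Primary endpoint analysis will be according to intention to treat with last observation carried forward for missing data". This fixes the analysis population and the handling of missing data, but not a model.
- **Covariates.** The next sentence is the only one on adjustment: "Failures of randomization would be adjusted for as factors or covariates, using generalized linear modelling".
- **Power.** "In each centre, with 30 families randomised to the control and intervention arms", the trial is said to detect effects of "0.8 or greater for change scores on continuously distributed outcomes", "at 80% power and 95% confidence".
- **Pooling.** Results from the centres are to be combined by meta-analysis.

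**The concern.** Adjusting when randomisation has failed makes sense only if the default model does not adjust. After sound randomisation, baseline differences are due to chance, so a rule triggered by them lets the data choose the model. No trigger or covariate list is given. The rule therefore leaves room for different models for different outcomes and centres, and those estimates would then meet in one meta-analysis.

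Two further costs follow from the implied default. A change score fixes the baseline coefficient at 1, which is less precise than estimating it whenever the baseline to six-month correlation is below 1. And when allocation is balanced on a prognostic variable that the analysis leaves out, the calculated standard error is too large for outcomes related to that variable. Here the variable is the baseline of a principal outcome.

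**Working it through.** **Inputs.** From the article: 0.8 SD of change, 80% power, 95% confidence (read as two-sided 5%), and 30 families (read as 30 per arm; the wording could also mean 30 in total). Assumed, because the article does not give them: baseline to six-month correlation r = 0.4 to 0.7, equal variances at both times, normal scores, and a strain stratum formed by a median split.

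**1. The plan's own figure.** n per arm = 2(1.960 + 0.842)² / 0.8² = 24.5, so 25 (26 by the t distribution). With 30 per arm, power for 0.8 SD is 86% by the noncentral t, and the effect detectable at 80% power is 0.736 SD of change. The target is met with some margin.

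**2. Outcomes not used for balancing.** Change-score variance is 2(1 − r)σ². Residual variance after adjusting for baseline is (1 − r²)σ². The ratio is (1 + r)/2, and the detectable effect is 0.736 × √ratio.

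| r | Variance ratio | Detectable effect (SD of change) | Power at 0.8 SD | Power at 0.5 SD |
|---|---|---|---|---|
| Change score | 1 | 0.74 | 86% | 48% |
| 0.4 | 0.70 | 0.62 | 95% | 62% |
| 0.5 | 0.75 | 0.64 | 94% | 59% |
| 0.7 | 0.85 | 0.68 | 91% | 54% |

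The 0.5 SD column is for illustration; it is not the article's target. The formula ignores the small cost of estimating the slope. In simulation at 30 per arm the ratios were 0.72, 0.76 and 0.86.

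**3. The strain outcome.** Balancing within a median split leaves only the within-stratum part of baseline variance free to differ between arms: k = 1 − 2/π = 0.363. In units of σ², and apart from the common factor 2/n:

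- true variance of the change-score difference: (1 − r²) + k(1 − r)²
- variance the unadjusted test assumes: (1 − r²) + (1 − r)² = 2(1 − r)
- adjusted relative to true change-score variance: (1 + r) / [(1 + r) + k(1 − r)]
- true relative to assumed variance: [(1 + r) + k(1 − r)] / 2

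| r | Adjusted / true change-score variance | True / assumed variance | Type I error of unadjusted test |
|---|---|---|---|
| 0.4 | 1.4/1.618 = 0.865 | 0.809 | 3.0% |
| 0.5 | 1.5/1.682 = 0.89 | 0.841 | 3.3% |
| 0.7 | 1.7/1.809 = 0.94 | 0.905 | 4.0% |

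The last column is 2·P(t₅₈ > 2.002/√(true/assumed)). Simulation (40,000 trials per setting) gave 3.0%, 3.3% and 4.1% for the unadjusted test, and 4.7–5.0% with baseline adjustment.

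**4. The conditional rule.** The article gives no trigger, so take one: adjust for the outcome's own baseline only if it differs between arms at p < 0.05. Type I error in the same simulations was 4.3–4.7% without stratification and 3.0–4.1% with it. In a separate simulation at 0.8 SD (4,000 trials per setting, r = 0.3 to 0.7), power was 87–90% for this rule and 91–97% for adjustment in every case.

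**5. How often chance alone would trigger it.** Four outcomes not used for balancing, in six countries, give 24 checks. If these were independent, 1 − 0.95²⁴ = 71% is the probability of at least one apparent failure under perfect randomisation. Independence is an assumption; correlated outcomes would lower the figure.

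**The case against.** **The unadjusted default is inferred.** The article never says that the primary analysis is unadjusted, and change scores appear only in the power statement. A before-and-after comparison could be analysed with the baseline as covariate, powering on change scores would then simply be conservative, and a full analysis plan could specify that. This stands as a limit on the wording: the default is implied, not declared. It does not remove the point, because the article is not silent. It states a conditional rule, and a plan with unconditional adjustment would contradict it.

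**A reader might infer an inflated error rate.** The documents do not support that. Under the one trigger tested, type I error is at or below 5%. Free choice among many covariates could behave differently, but the article names none and it was not tested.

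**A reader might infer that the trial is biased or too small.** Neither follows. Randomisation protects the comparison on average, and the 0.8 SD target is met at 30 per arm. If 30 were the total, power would be 56%, but that is a question about the sample-size wording, not about adjustment.

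**A reader might apply a 25% variance saving to every outcome.** It does not carry over to strain. Large chance imbalance on strain is largely designed out, so the estimator gains only about 6–13%. Most of what adjustment brings there is a correct standard error.

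**Different models by outcome and centre** are something the rule permits, not something the article announces.

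**Conclusion.** The point holds in a limited form. The article fixes a covariate rule that depends on the data and is undefined, and by implication leaves out two variables that should be in the model from the start.

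The consequences are lost precision, a conservative test of the strain outcome, and room to choose covariates after seeing imbalance. For the four outcomes not used for balancing, the detectable effect is 0.74 SD of change where 0.62–0.68 was available. For strain, the true variance ratio is about 0.865–0.94 and type I error about 3–4%. No stated design claim fails.

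These sizes rest on r between 0.4 and 0.7, equal variances, 30 per arm and, for strain, a median-split stratum. None of r, the variances or the form of the stratum is in the article. The gain shrinks as r approaches 1. The correction is worth making because it costs almost nothing.

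**What to change.** Delete the sentence on failures of randomisation. In its place, state that within each centre, and whatever the observed balance, each principal outcome is analysed by a linear model of the six-month score on arm, that outcome's baseline score and the caregiver-strain factor used in randomisation. State that the adjusted centre estimates then enter the meta-analysis already planned. A single pooled model with centre as a covariate is not needed and would depart from that plan.

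The cost is wording only. The baseline scores are already collected before randomisation, and the strain factor is known from the allocation.
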